### Outcome measures

The primary outcome is HbA1c after 6 months. HbA1c is chosen as it is currently the most commonly used diagnostic test for pre-diabetes and T2DM in New Zealand [40], and therefore has the most direct relevance to clinical practice.

Secondary outcomes include HbA1c after 3 months and 9 months, which is 3 months after the cessation of the interventions to check if there are persistent effects. Other secondary outcomes include fasting glucose, insulin resistance measured by homeostatic model assessment, fasting lipid profiles, mean systolic and diastolic blood pressure, and anthropometric measures (waist size, body weight, and body mass index (BMI)) at 3 and 6 months. Psychological outcomes include symptoms of depression, anxiety, and stress measured on the shortened version of the Depression Anxiety Stress Scale (DASS 21) [41] and health-related quality of life measured by the short-form health survey version 2 for New Zealand/Australia (SF-36) [42] after 6 and 9 months only. See Table 1 for a summary of outcome measures, and Table 2 for a summary of questionnaire variables. Study questionnaires were pre-tested during the study set up.

**Table 1 Tab1:** Summary of outcome measures

Outcomes	Time point	Measurement
Primary outcome		
HbA1c	At 6 months	Measured from whole blood from K_2_EDTA tube on a Cobas c 311, Roche Diagnostics, Auckland, New Zealand
Secondary outcomes		
HbA1c	At 3 and 9 months	Measured from whole blood from K_2_EDTA tube on a Cobas c 311, Roche Diagnostics, Auckland, New Zealand
Fasting plasma glucose	At 3, 6, and 9 months	Measured from plasma from fluoride/oxalate tube on a Cobas c 311, Roche Diagnostics, Auckland, New Zealand
Fasting insulin		Measured from plasma from K_2_EDTA by Human/Canine/Porcine Insulin DuoSet ELISA R&D Systems Inc.
HOMA-IR		Calculated as HOMA = (glucose (mmol/l) x insulin (pmol/l))/22.5 [43]
Fasting lipid profiles		Measured from fasting serum from SST II Advance Tube as total cholesterol, low-density lipoprotein cholesterol, high-density lipoprotein cholesterol, and triglycerides. Measured on a Cobas c 311, Roche Diagnostics, Auckland, New Zealand
Blood pressure	At 3 and 6 months	Measured as mean systolic and mean diastolic blood pressure using standard calibrated electronic sphygmomanometer and protocol*
Weight		Measured in kg using standard calibrated electronic equipment and protocol*
Waist circumference		Measured in cm using standard equipment and protocol*

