### Analysis plan

All primary analyses will be based on intention-to-treat principles with all individuals analysed in the group to which they were randomized. Demographic and baseline characteristics will be summarised using descriptive statistics. The primary outcome is HbA1c at 6 months. The primary analysis for the main outcome variable will be analysis of covariance (ANCOVA) with the baseline measurement of HbA1c as a continuous covariate, and the randomized treatments as main effects, and their interaction as categorical explanatory variables. Adjusted analyses will be conducted to include potential baseline confounding variables (BMI, level of exercise and total daily energy intake), and whether medications that could affect glucose metabolism were used after randomization. The effect of change in weight, change in exercise, and change in total daily energy intake between baseline and 6 months on HbA1c will also be explored using ANCOVA. A linear mixed model using all of the three HbA1c measurements and an appropriate random effects structure to account for correlation between repeated measurements, and using HbA1c at baseline as a continuous covariate, will be used as a sensitivity analysis for the effect of the randomized treatments. Subgroup analysis will use interaction terms (with treatment) for whether treatment effects vary by ethnicity, sex, or socioeconomic status.

Secondary outcome variables will be analysed in a similar way, with the most important outcomes for each being the 6-month time point. All outcome variables will be analysed with their baseline value as a continuous covariate. Subsequent sensitivity analyses will be guided by the outcome of this, with the introduction of relevant baseline covariates for each outcome variable. Factors which may affect mental health and well-being outcomes such as alcohol, recreational drug use, and life stressors will be described and considered in the analysis. Additional file 3 contains tables for baseline characteristics and results.

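### Table 1's HOMA-IR formula pairs insulin in pmol/l with 22.5, the divisor for insulin in mU/l; applied as printed, it gives values about 6 to 7 times too high

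*Protocol article*

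**What the plan says.** The Outcome measures section of the protocol article includes "insulin resistance measured by homeostatic model assessment" among the secondary outcomes. The HOMA-IR row of Table 1 gives the derivation: "Calculated as HOMA = (glucose (mmol/l) x insulin (pmol/l))/22.5". The fasting insulin row of the same table describes the assay, "Measured from plasma from K_2_EDTA by Human/Canine/Porcine Insulin DuoSet ELISA R&D Systems Inc", but gives no reporting unit. The unit in the HOMA-IR row is therefore the only insulin unit in the article. No other section gives a conversion between pmol/l and mU/l, or a different divisor.

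Under Analysis plan, secondary outcomes are handled in a similar way to the primary, and "All outcome variables will be analysed with their baseline value as a continuous covariate".

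**The concern.** The divisor in this index is not arbitrary. It scales the result to 1 at a reference point, so it is tied to the units of both inputs. The printed glucose unit fits 22.5; the printed insulin unit does not.

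If someone codes the outcome from Table 1 with insulin in pmol/l, the published HOMA-IR levels, the adjusted differences between arms and their confidence limits will all be on the wrong scale. Baseline values would make the participants look implausibly insulin resistant. Neither the levels nor the absolute effect could be set beside other studies or a recognised cut-off. Significance tests would give no warning, because a constant multiplier does not change them.

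**Working it through.** **Inputs from the article.** Glucose in mmol/l, insulin in pmol/l, divisor 22.5 (Table 1, HOMA-IR row). Analysis by a model with the baseline value as covariate (Analysis plan).

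**Inputs assumed.** Neither of these is in the article.
- The standard normalisation of the index: HOMA-IR = 1 at glucose 4.5 mmol/l and insulin 5 mU/l.
- The conversion factor k, in pmol per mU: 6.0 to 6.945, the range of usual values. An older value of 7.175 is carried as an upper check.

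**Step 1: reproduce the divisor.** 4.5 × 5 = 22.5. The article's constant is recovered exactly, but with insulin in mU/l.

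**Step 2: apply the printed formula at the reference point.** Insulin of 5 mU/l is 5 × 6.0 = 30.0 pmol/l, or 5 × 6.945 = 34.7 pmol/l.
- 4.5 × 30.0 / 22.5 = 6.0
- 4.5 × 34.725 / 22.5 = 6.945

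The index should be 1.0 here. At k = 7.175 it would be about 7.2.

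**Step 3: show that the ratio is constant.** As printed, the index is glucose × (k × insulin in mU/l) / 22.5. Correctly, it is glucose × insulin in mU/l / 22.5. The ratio is k whatever the glucose and insulin values.

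**Step 4: illustrative participants (values chosen for illustration).**

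| Glucose (mmol/l) | Insulin (mU/l) | Correct | As printed, k = 6.0 | As printed, k = 6.945 |
|---|---|---|---|---|
| 5.5 | 10 | 2.44 | 14.67 | 16.98 |
| 5.8 | 12 | 3.09 | 18.56 | 21.48 |
| 6.0 | 15 | 4.00 | 24.00 | 27.78 |

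**Step 5: work backwards.** For the printed formula to give 1 at glucose 5.5 mmol/l, insulin must be 22.5 / 5.5 = 4.1 pmol/l. That is 4.1 / 6.945 = 0.6 to 4.1 / 6.0 = 0.7 mU/l, far below the reference of 5 mU/l.

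**Step 6: the divisor that fits pmol/l.** 22.5 × 6.0 = 135 and 22.5 × 6.945 = 156.3 (161.4 at k = 7.175).

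**Step 7: effect on the planned analysis.** One simulated data set with 152 participants, 76 in each of two arms, was analysed by ANCOVA with baseline as covariate. Baseline and outcome were then both multiplied by k.

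| Multiplier | Adjusted difference | P value |
|---|---|---|
| 1 | −0.367 | 0.0083 |
| 6.0 | −2.202 | 0.0083 |
| 6.945 | −2.549 | 0.0083 |

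The difference scales by exactly k (−2.202 / −0.367 = 6.0) and the P value does not move. Confidence limits scale by the same factor, because the standard error does. Ratios between arms, or to baseline, are unchanged because k cancels.

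**The case against.** The strongest reply is that this is one unit label in one cell of a summary table. The article shows neither the derivation code nor the unit in which the assay results are entered. If insulin is in fact entered in mU/l, the computed values are right and only the label is wrong. That reply stands. A reader might infer from Table 1 that every reported HOMA-IR value will be wrong; the article supports only the conditional statement that they will be wrong if the formula is followed as printed.

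The reply also limits what is at stake. The primary outcome is HbA1c at 6 months. HOMA-IR plays no part in eligibility, sample size or data monitoring. The Economic analysis section draws its effect estimates from HbA1c, BMI, blood pressure and total cholesterol. No cut-off or responder definition based on HOMA-IR is planned, so the loss of comparability concerns later interpretation. An inflated result could be put right at any time by dividing by one constant.

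A reader might also infer that the error would go unnoticed because the P values do not change. That goes too far. Baseline characteristics are to be summarised descriptively, and if HOMA-IR is among them, a level of 15 to 17 where about 2.4 is expected could alert the team. The table shells are in Additional file 3, which is not shown.

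Finally, a reader might want to move the analysis to the log scale, where the constant drops out of the treatment effect. That is a separate choice, commonly left to the statistical analysis plan, and it would leave the reported levels wrong.

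The reply does not remove the mismatch itself. The row is legible, the formula is explicit, and nothing elsewhere in the article reconciles the unit with the divisor.

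**Conclusion.** The printed unit and divisor do not belong together. Applied as printed, the formula multiplies every HOMA-IR level, mean difference and confidence limit by the pmol-per-mU factor: about 6 to 7 times, assuming 6.0 to 6.945. This rests on the standard 4.5 × 5 normalisation and on that assumed range, neither of which is in the article. That the two cannot both stand does not depend on the exact factor.

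The harm is conditional on insulin in pmol/l actually being entered; the article cannot settle whether the unit is a misprint. No conclusion about whether an effect exists would change, and neither the primary outcome nor the economic model is touched. It is a definite error in the definition of a secondary outcome and should be corrected, but it does not threaten the trial's main result.

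**What to change.** State one matching pair in Table 1 and wherever the outcome is defined for analysis:

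- insulin converted to mU/l, naming the conversion factor used for this assay, with divisor 22.5; or
- insulin in pmol/l, with divisor 22.5 times that factor (about 135 to 156 for factors of 6.0 to 6.945).

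Give the reporting unit in the fasting insulin row as well. Then check that the derivation code uses the same pair. A simple test is that glucose 4.5 mmol/l with insulin equivalent to 5 mU/l returns 1.0.

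The cost is one line of text and a check of the code. No new data are needed. If values have already been derived with pmol/l and 22.5, dividing them by the conversion factor puts them right.

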### Randomization and blinding

Randomization will be performed independently by Fonterra Co-Operative Ltd, using Microsoft Excel and a computer-generated random number list according to procedures explained by Kim and Shin [35]. Randomization will be performed in blocks of eight and not stratified; however, covariates will be collected and an important selection of these will be used in a sensitivity analysis.

The study is double-blinded for study capsules and only the study statistician will be unblinded after data analysis of the 6-month primary outcome. Outcome assessors and all participants will remain blinded to capsule allocation until all 9-month follow-up data are collected. Due to the obvious difference in cereals the study is not blinded for cereals; however, participants will not be informed of the full rationale for cereal choices, the full contents of cereal packages, or which cereal is considered the intervention and which is the control until after all participants have completed the study.

Fonterra Co-Operative Ltd will share the study cereal allocation codes with the study centre, while capsule allocations will remain double-blinded until data are analysed.

Staff will allocate the next study number in consecutive sequence to those eligible at the commencement of the enrolment visit. The type of cereal allocated will only be revealed to the participant at the time the relevant intervention is dispensed after baseline measures are collected.

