#### Adverse effects and modification to study interventions

In previous HN001 studies we have found the probiotic to be safe and well tolerated [20, 39].

All components of the cereal interventions are marketed for human consumption and are therefore not a safety risk. While some individuals require gradual increases when introducing a higher level of fibre into their diet, consumption up to 10 g β-glucan daily is generally tolerated [30]. β-glucans undergo fermentation in the colon, and participants may experience flatulence, bloating, or alteration in bowel habits [30]. Any gastrointestinal effects of interventions will be systematically assessed in questionnaires included in the 3-, 6-, and 9-month follow-up visits.

If any participant reports gastrointestinal symptoms which may relate to the study interventions that are causing discomfort, pain, or impacting on the participant’s ability to take the study interventions, and are not severe enough to require medical review, the following procedure will be followed:Discontinue both capsule and cereal interventions until symptoms settle. In instances where participants clearly relate symptoms to the cereal then they stop the cereal only and continue with the capsule.If symptoms resolve, then they recommence capsules only and continue for a few days to check that no symptoms return.If capsules are tolerated, they begin to reintroduce the cereal. Start the cereal reintroduction by mixing powder with cereal and taking half of the total dose only. Then, after a few days and if tolerated well, gradually increase the dose to the full amount.If at any point symptoms return, they reduce the dose to the level that they can tolerate.If required, to improve tolerability the daily cereal dose may be taken in part doses spread over the day.It is very unlikely that participants would not be able to tolerate either of the interventions; however, should this occur the participant will be encouraged to continue in the study with interventions at levels they can tolerate, and to ensure outcome data are collected for an intention-to treat analysis. Compliance with the interventions will be collected (see below).If symptoms do not resolve on discontinuation of study capsule and cereals, then advise participant to see their usual healthcare provider for further advice and investigation; withhold study interventions until a diagnosis is made and the symptoms are resolved. Then consider reintroduction as per 2–5 above.

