Body mass index		Calculated as weight (kg)/height (m)^2^
Depression, anxiety, and stress scores	At 6 and 9 months	Measured using DASS 21. The DASS is a set of three self-report scales designed to measure states of depression, anxiety and stress. It has validated psychometric properties, with good test–retest properties in both clinical and community populations, and is robust across a range of demographic variables [44–48]
Physical and emotional well-being		Measured using SF-36. The SF-36 is a self-completed questionnaire, relating to physical and emotional health over the past 4 weeks. It is a well-validated scale, with good psychometric properties, widely used as a health outcome measure [42, 49–51]. Raw data will be uploaded and analysed on the ‘QualityMetric Health Outcomes TM scoring software 5.1. Permission to use granted on 13 December 2017
Other outcomes		
Adverse events	At 3, 6, and 9 months	Hospitalizations
		Gastrointestinal symptoms and bowel function
Compliance	At 3 and 6 months	Calculated based on return of unused cereal and capsules

*See Additional file 2 for equipment and protocols for anthropometric and blood pressure measures

*DASS 21* Shortened version of the Depression Anxiety Stress Scale, *HbA1c* glycated haemoglobin, *HOMA-IR* homeostatic model assessment of insulin resistance, *SF-36* Short-form health survey version 2 for New Zealand/Australia

**Table 2 Tab2:** Summary of questionnaire variables

Questions	Time point collected	Details	Source
Demographics	Baseline	Name, address, date of birth, ethnicity, income, educational qualifications	Questions based on Statistics New Zealand Census questions 2013, available from http://archive.stats.govt.nz/Census/2013-census/info-about-the-census/forms-guidenotes.aspx.
Diabetes and cardiovascular disease risk factors	Baseline	History of first-degree relative with type 2 diabetes mellitus. Personal history of gestational diabetes, or polycystic ovarian disease (females only), hypertension, dyslipidaemia, myocardial infarction, stoke, mental illness, ethnicity, smoking	Questions based on Ministry of Health 2016 New Zealand Health Survey Adult Questionnaire (Year 6) 1 July 2016–30 June 2017 with some specific additions. New Zealand Health survey available from https://www.health.govt.nz/publication/content-guide-2016-17-new-zealand-health-survey

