Physical activity measure	All	Six-point descriptive categorical scale used to assess levels of activity, and in relation to recommended activity guidelines. Categories broadly match activity intensity based on metabolic equivalents.	Stanford Leisure-Time activity categorical Item (L-Cat 2.2) [38]
Smoking	All	Classification as non-smoker, ex-smoker, or current smoker and intensity of current smoking	Developed by researchers
Alcohol and recreational drug use	Baseline and at 6 and 9 months	Frequency of alcohol use and number standard drinks taken of a typical day. Use of substances for recreational or non-medicinal purposes to get high. Identifies substances used and frequency of use	Questions based on Ministry of Health 2016 New Zealand Health Survey Adult Questionnaire (Year 6) 1 July 2016–30 June 2017 with some specific additions. New Zealand Health survey available from https://www.health.govt.nz/publication/content-guide-2016-17-new-zealand-health-survey
Gastrointestinal symptoms	At 3, 6 and 9 months	Changes in frequency of gastrointestinal symptoms including nausea/vomiting, stomach aches, cramps, or pain, bloating or swollen stomach/abdomen, and bowel motions. Evaluation of impact of any changes in bowel pattern.	Developed by researchers
Hospitalizations	At 3, 6 and 9 months	Hospitalizations since previous visit (excluding elective surgery and outpatient appointments)	Developed by researchers
Use of reduced dose of cereals	At 3 and 6 months	Yes/no question to determine if participant usually takes half or less of the daily dose of corn/oats, and powder sachet	Developed by researchers

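### Gut symptoms, the main anticipated harm of the β-glucan cereal, are collected only as self-reported change after baseline, so the cereal comparison rests on recall by participants who can see their cereal

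*Protocol article*

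**What the plan says.** Under Adverse effects and modification to study interventions, the protocol article expects that with β-glucan "participants may experience flatulence, bloating, or alteration in bowel habits". No other side effect is anticipated there. The same section says that gut effects "will be systematically assessed in questionnaires included in the 3-, 6-, and 9-month follow-up visits".

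Table 2 (Outcome measures) describes the item as "Changes in frequency of gastrointestinal symptoms including nausea/vomiting, stomach aches, cramps, or pain", continuing with bloating and bowel motions, and sets its time point as "At 3, 6 and 9 months". The researchers wrote the item themselves and its wording is not shown. Table 1 places "Gastrointestinal symptoms and bowel function" with hospitalizations as the adverse events, under other outcomes.

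Data and sample collection lists the bowel symptom questions among those that participants complete themselves online. Randomization and blinding states: "Due to the obvious difference in cereals the study is not blinded for cereals". It adds that participants are not told which cereal is the intervention, that capsules are double-blind, and that the cereal is revealed only after baseline measures are taken.

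**The concern.** A harm comparison is strongest when the same question is asked before and after allocation, and when knowledge of allocation cannot colour the answer. Here the gut item has neither safeguard for the cereal factor. There is no recorded starting level, the participant judges the change, and the participant knows whether the daily serving is oats or cornflakes.

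What is at stake is the tolerability statement for the β-glucan cereal, which feeds the trial's aims on acceptability and implementation. If oat recipients attribute more, or less, of their ordinary gut experience to the cereal than cornflake recipients do, the difference between arms mixes effect with reporting, and no baseline value helps to separate them.

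**Working it through.** **1. Is the missing baseline a matter of condensing?** No. Table 2 is the collection schedule for questionnaires. It marks other rows as baseline, as all time points, or as baseline plus later visits. The gut row has follow-up times only, and the adverse-effects text gives the same three. Table 1 is not used as evidence, because it lists only follow-up times for every outcome, HbA1c included.

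**2. What does change refer to?** The gut row gives no reference period. Two readings are possible:
- *Since the preceding visit.* A symptom that starts early and persists is a change at 3 months but can be answered as no change at 6 months, so it would be missed there.
- *Since before the study.* Persistent symptoms are captured, but the participant must recall a state 3, 6 or 9 months back, with no recorded value to check against.

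Each reading has a weakness that an absolute-frequency question would avoid.

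**3. How much could differential reporting matter for the cereal factor?** The plan states no symptom rate, power or sample size for this outcome, so there is no figure to reproduce. The following is an illustration under assumptions.

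From Sample size: 38 per factorial combination gives 2 × 38 = 76 per cereal arm; less the plan's 25% drop-out, 76 × 0.75 = 57. Assumed: no true effect, a two-sided 5% test, a true rate p₁ in both arms, and over-reporting in the oat arm so that its reported rate is p₂.

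Chance of a significant oat excess = Φ{ [(p₂ − p₁) − 1.96 √(2p̄(1 − p̄)/n)] / √([p₁(1 − p₁) + p₂(1 − p₂)]/n) }, where p̄ is the mean of p₁ and p₂.

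For p₁ = 0.20, p₂ = 0.30, n = 57: p̄ = 0.25; √(2 × 0.25 × 0.75/57) = 0.0811, times 1.96 = 0.159; √((0.16 + 0.21)/57) = 0.0806; (0.100 − 0.159)/0.0806 = −0.73; Φ = 0.23.

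| True rate, both arms | +5 points | +10 points | +15 points |
|---|---|---|---|
| 10% | 12% | 32% | 56% |
| 20% | 9% | 23% | 43% |
| 30% | 8% | 20% | 38% |

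Without differential reporting the chance in that direction is 2.5%. With all 76 per arm retained, the range is 9.6% to 68.5%.

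**4. What does the missing baseline cost in precision?** For a symptom score whose correlation between baseline and follow-up is ρ, adjustment leaves 1 − ρ² of the variance. For assumed ρ of 0.3, 0.5 and 0.7 this is 0.91, 0.75 and 0.51. That gain is forgone for both factors, HN001 included.

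**The case against.** The case on the other side is substantial, and several stronger readings fall to it.

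- *Reference period.* A reader might infer that the reference point moves from visit to visit, because nearby Table 2 rows on hospitalizations, foods and stress events count from the preceding record. With an assumed 20% onset and three quarters persisting, 0.20 × 0.75 = 15% would have symptoms at 6 months while about 0% would be recorded as new. The gut row does not carry that interval, the questionnaire is not shown, and both rates are assumed. If the item refers to the pre-study state, the calculation fails.
- *HN001.* A reader might extend the recall concern to the probiotic. Capsules are double-blind with an identical-looking placebo, so recall error should not differ by capsule.
- *Open label.* Participants are not told which cereal is active, its full contents or the full rationale, and the control serving also includes a powder. Masking is partial, and no text shows that oat recipients expect gut effects. Differential recall is a risk, not a demonstrated bias.
- *Conflict with the Analysis plan.* The sentence "All outcome variables will be analysed with their baseline value as a continuous covariate" might be read as a requirement that the gut item cannot meet. It stands in the paragraph on secondary outcomes, whereas Table 1 classes gut symptoms as an other outcome beside compliance, which cannot have a baseline value either. The documents do not support calling this a contradiction.
- *Randomization.* If recall is equal across arms, comparing reported change remains valid in expectation, and pre-existing symptoms are balanced on average.
- *Other sources.* The 2-week contact, counts of returned product, the reduced-dose question and monthly review of stopping all bear on tolerability.

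What remains is that none of these other sources is described as a baseline symptom measure, and the interviews cover only the β-glucan arms, so they offer no comparison. The equal-recall assumption is weakest for the cereal factor, the one for which gut effects are expected.

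**Conclusion.** The point holds as a weakness in how a harm is measured. By stated schedule, the main anticipated harm of the β-glucan cereal is a self-reported recalled change with no baseline, given by participants who can see their cereal. The cereal comparison is exposed to differential recall and cannot be adjusted for pre-existing symptoms. The HN001 comparison loses precision but is not exposed in that way while the capsule blind holds. The HbA1c primary outcome is untouched.

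The size is unknown from the documents. The 8% to 56% chance of a spurious excess (57 per arm) depends on assumed symptom rates of 10% to 30% and assumed over-reporting of 5 to 15 points; with equal reporting there is no excess risk. The unstated reference period adds uncertainty, but loss of persistent symptoms at 6 months follows only under one of its two readings.

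**What to change.** **Change.** In Table 2, set the gut-symptom row to all time points and record frequency over a fixed recent period in place of change. Give the baseline questionnaire before the cereal is revealed, which the existing visit order allows. Compare arms at each follow-up time adjusted for the baseline value. Name flatulence among the items: the adverse-effects text expects it, but the Table 2 list does not mention it.

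**Participants already enrolled.** Recruitment began in February 2018 with completion expected around April 2019 (Trial status), so many or all may have passed baseline. For them, keep the change item alongside the frequency item, with its reference period fixed to the pre-study state. Report the cereal comparison as unblinded self-reported change.

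**Cost.** A few extra self-completed questions per time point. Participants enrolled before the amendment will lack the baseline value, and their earlier answers on change are not comparable with the frequency item. The two measures should be reported separately. If no one remains to be enrolled, the baseline cannot be recovered; what is left is to state the reference period, add absolute frequency at any remaining time points, and report the limitation.
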